## REVISION HISTORY

| Revision # | Version Date | Summary of Changes                        |
|------------|--------------|-------------------------------------------|
| 2          | 2/22/22      | Incororated all clarifications, spelling. |
|            |              |                                           |
|            |              |                                           |
|            |              |                                           |
|            |              |                                           |

## Study Summary

|                                                   |                                                                                                                                                                                                                                                               |
|---------------------------------------------------|---------------------------------------------------------------------------------------------------------------------------------------------------------------------------------------------------------------------------------------------------------------|
| Project Title                              | InPART Rx - Inpatient Provider Antibiotic Rate Benchmarking to Reduce Unnecessary Prescribing                                                                                                                                                                 |
| Project Design                             | 
Phase 1: Retrospective analysis of summary encounter data by prescriber
 
Phase 2: Prospective evaluation of impact of quality-improvement activity composed of feeding back peer comparison data on antibiotic prescribing to prescribers
        |
| Primary Objective                          | Determine the impact of using an automated peer comparison of antibiotic prescribing on hospitalists' prescribing rates                                                                                                                                       |
| Secondary Objective(s)                     | 
Determine variability and predictors of antibiotic prescribing by Hospital Medicine Service (HMS) across four Emory Healthcare Hospitals
 
Demonstrate no adverse effects on patients cared for by HMS during study period
                        |
| Research Intervention(s)/Interactions      | Provide messaging bi-monthly to hospitalists via email that contains peer comparison data and antibiotic prescribing educational content                                                                                                                      |
| Study Population                           | Primary population is all Hospital Medicine Service (HMS) Providers at EUH, EUHM, EJCH, ESJH.                                                                                                                                                                 |
| Sample Size                                | Including 147 HMS providers, accounting for cluster effect we should be able to detect a large effect size (.9 to 1.1) with 80% statistical power. This translates to reductions in prescribing rates of 10% during intervention period from baseline period. |
| Study Duration for individual participants | October 2022 – December 2024                                                                                                                                                                                                                                  |

|                                                  |                                                                                                                                                                  |
|--------------------------------------------------|------------------------------------------------------------------------------------------------------------------------------------------------------------------|
| Study Specific Abbreviations/ Definitions | Hospital Medicine Service (HMS)
Standardized Antibiotic Prescribing Ratio (SAR)
C. difficile infection (CDI)
Days of Therapy (DOT)
Patient-days (PD) |
| Funding Source (if any)                   | Centers for Disease Control and Prevention                                                                                                                       |

## Objectives

Primary Objective: **Determine the impact of using an automated peer comparison of antibiotic prescribing on hospitalists' prescribing rates**

Secondary Objectives:

- 1) Demonstrate no adverse effects on patients cared for by HMS during study period
- 2) Determine variability and predictors of antibiotic prescribing by Hospital Medicine Service (HMS) across four Emory Healthcare Hospitals

## Background

Approximately 50% of hospitalized patients receive an antibiotic during their stay.(A) Currently >75% of hospitals, including all highly ranked academic medical centers, employ hospitalists who increasingly provide care for inpatients and represent a prime target for inpatient antibiotic stewardship efforts.(B,C) Hospitalists care for newly admitted patients and those transitioning from critical and long term care, and frequently prescribe antibiotics for common inpatient problems (e.g., urinary tract infection, pneumonia). Recent studies of antibiotic prescribing data for these conditions suggest opportunities to improve prescribing accuracy: an estimated 30% of antibiotics used for these common infections were either unnecessary or prescribed incorrectly (D). In the ambulatory setting, there is substantial evidence that improving provider prescribing practices can be achieved by using peer comparisons of provider-specific antibiotic prescribing rates for benchmarking and feedback (E,F,G,H). Similarly, in the ambulatory setting Emory Healthcare (EHC) through a Quality Initiative (QI) has successfully used peer comparisons of clinic-specific and provider-specific prescribing metrics and targets (I).

The Study team has expanded this QI to the inpatient setting by exploring provider-specific prescribing metrics for EHC hospitalists. The goal of this QI work is to use traditional QI methods of peer-comparison through data feedback to improve antibiotic prescribing among EHC HMS by reducing unnecessary antibiotic use and improve patient safety on the

EHC HMS. This protocol outlines discrete steps taken to evaluate the impact of this expanded QI effort.

Our work is dedicated to delineating and implementing successful peer comparisons using a novel provider-specific prescribing metric – standardized antibiotic prescribing ratio (SAR) which relies on direct standardization based on patient mix indicators (M). We are also studying the relationship between changes in providers' SAR on patient outcomes. To date, the impact of hospital medicine peer comparisons on antibiotic prescribing or patient outcomes of such efforts have not been formally studied. We wish to evaluate the impact of this QI initiative and believe the results may contribute to generalizable knowledge of this process.

Preliminary data: Billing data combined with electronic antibiotic administration data and patient clinical data was used to produce a SAR for hospitalists at each of 4 EHC hospitals from January 2016 to December 2018. Direct standardization was accomplished by creating regression models to adjust for patient-level factors (age>65 years, Comorbidity Index; end stage renal disease, malignancy, pneumonia, urinary tract infection and sepsis), with data aggregated over 2-month periods; 116 hospitalists contributed to 437,303 billed patient-days. After adjustment by patient mix and entity, SAR variation remained (interquartile range of SAR 0.9-1.1) suggesting variations due to hospitalist behavior (i.e., knowledge, comfort, conformity) drive differences (K). These analyses need to be repeated during COVID-19 pandemic period to be relevant for a QI initiative in late 2022.

## Study Endpoints

Primary: Change in SAR (i.e., standardized Observed: Expected ratio) (HMS provider data)

Specifically, change in median bi-monthly SAR values among all participating HMS providers between intervention and pre-intervention periods (accounting for facility effect and patient mix).

Secondary

- CDI (C. difficile infection) events among HMS patients: Likelihood (rate ratio) of CDI occurring in any HMS patient in post-intervention period is less than or equal to 1.0 (no different from baseline or protective)
- LOS (Length of stay): model attributable LOS for each HMS patient, comparing estimates of intervention period on attributable LOS.

- Readmissions: model probability of patient having readmission, and impact of intervention on readmission rates among all HMS patients, as well as stratified by providers with large reductions in SAR compared to those without large reductions in SAR.

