## Procedures Involved

Design. We will employ a quasi-experimental before-after study design, using a stepped wedge approach with 4 hospitals. Study participants will include all 147 full-time hospitalists. The intervention will be rolled out sequentially to all 4 hospitals in 3-month intervals. The intervention will last 18 months at all 4 sites.

Figure - Enrollment – facilities (EHC Entity) will be randomized to order of implementation roll out of intervention (INT), or continue baseline (BSLINE) usual care. Interim analysis (IA) would occur after 3 quarters of intervention to assess need for secondary intervention.

| EHC Entity | 18 months retrospective | QTR3   | QTR4   | QTR1   | QTR2   | QTR3   | QTR4   | QTR1  | QTR2-3 |
|------------|-------------------------|--------|--------|--------|--------|--------|--------|-------|--------|
| First      | BSLINE                  | INT    | INT    | INT    | IA+INT | INT    | INT    | INT   | INT    |
| Second     | BSLINE                  | BSLINE | INT    | INT    | INT    | IA+INT | INT    | INT   | INT    |
| Third      | BSLINE                  | BSLINE | BSLINE | INT    | INT    | INT    | IA+INT | INT   | INT    |
| Fourth     | BSLINE                  | BSLINE | BSLINE | BSLINE | INT    | INT    | INT    | IA+NT | INT    |

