## Analysis Plan and Outcomes.

Primary outcome is the provider-specific SAR, separately for each antibiotic grouping. Secondary outcomes include CD, readmission (< 30 days of discharge), length of stay. Changes in 2-month SAR will be estimated using an interrupted time series analysis, evaluating changes in each antibiotic grouping separately, analysis will consider hospital fixed effects. Secondary outcomes will be analyzed at the patient level among all billed encounters using logistic or negative binomial regressions. Inclusion of provider and quarter-year fixed effects will control for time-invariant provider and site characteristics and secular time trends (e.g., seasonal patient mix) and establish a difference-in-difference framework. This approach will estimate the within-provider change in patient outcomes, pre- and post-intervention. We will control for patient (e.g., sex, age, Comorbidity Index) mix, time-variant provider (e.g., census) factors.

Data Sources: The primary source of data will be the EH Clinical Data Warehouse (CDW), a repository that integrates data from multiple clinical applications within EHC and has flexibility to create customized, research-specific metrics. Outcomes for Aim 2 will also be calculated from data elements within the EH CDW (i.e., re-admissions, length of stay.)

Provider-specific SARs. Data elements will be aggregated into 2-month intervals for each of the 147 hospitalists across each hospital. Billed Days of Therapy (bDOT) and billed patient-days (bPD) derived for each antimicrobial group will be limited to the eligible dates of each patient encounter to dates billed by a hospitalist (bPD). For each period, a SAR will be determined from provider specific bDOT calculated along with predicted DOT using preliminary regression models. Regression models will be created from analyzing summary provider specific data and providers' encounter data for each 2-month period of the baseline period. Encounter summary data will be aggregate number of encounters billed by

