### 3. Study Design

We plan to use a Randomized Step Wedge Cluster Design (R-SWCD) to evaluate the effect of the peer comparison feedback report on antibiotic prescribing (BS-HO group). The study will be conducted in 4 hospitals (clusters) in Atlanta, Georgia. Of note, pending discussion with Hospital Medicine Leadership, the intervention may also be rolled out at an additional hospital, although lack of retrospective data would not allow inclusion of this facility in the full analysis. Hospitals will begin in the control condition and end in the intervention condition, wherein, all hospitals will receive the intervention and cross over to the intervention arm in a random order (Figure 1). Randomization will occur at the hospital level rather than at the provider level to avoid contamination and spillover effects. Providers within a hospital are not fully independent of each other, groups tend to form because of certain selection factors, and so providers tend to be more similar to each other with respect to potential confounders.

Outcomes linked to the same provider will be assessed repeatedly on a bi-monthly bases in each hospital over a two-year time period (2023-2024). Hospitals will cross-over to the intervention arm sequentially, resulting in 4 steps with an equal step length of 2 months. Following a baseline period (January 1 - June 30, 2023), the first cluster will begin the intervention on July 1, 2023. The final cluster will transition by March 1, 2024, with intervention continuing through December 31, 2024 in all hospitals.

A step wedge design, which involves the randomized and sequential roll out of the intervention to hospitals over time was chosen as it can model and adjust for any underlying temporal trends and results in all hospitals receiving the intervention **which is desirable from a healthcare quality improvement and antimicrobial stewardship perspective**. Randomization of the order of implementation reduces confounding from baseline cluster-level factors. Lastly, gradual roll out of the intervention will allow us to identify and address any implementation bottlenecks.

**Figure 1.** Stepped-Wedge interventional study design. Abbreviations: E, educational session; PF, Provider Feedback. Grey boxes reflect intervention periods with bi-monthly PF reports.

|            | 2023       |        |        |        | 2024   |        |               |
|------------|------------|--------|--------|--------|--------|--------|---------------|

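### Readmission is compared across strata defined by each provider's own later SAR reduction, with no cut-off, so the contrast cannot be read as an intervention effect or as evidence of safety

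*Combined protocol and SAP*

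**What the plan says.** The protocol's Study Endpoints section makes readmission a secondary endpoint with two parts: the "impact of intervention on readmission rates among all HMS patients", and the same outcome "stratified by providers with large reductions in SAR compared to those without large reductions in SAR". It gives no threshold for a large reduction and no handling of measurement error in the SAR. The Background gives the motive: "We are also studying the relationship between changes in" providers' SAR and patient outcomes. Under Analysis Plan and Outcomes, secondary outcomes are modelled at patient level with provider and quarter-year fixed effects and patient covariates.

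The SAP keeps 30-day readmission as a safety outcome (section 6), restricted to patients with codes for the targeted infections, and fits mixed-effects logistic models for the intervention effect (section 7). It has no strata by change in SAR or observed-to-expected ratio (OER), and section 5 keeps OERs out of the regression outcomes. It does not say that the protocol's stratified analysis is dropped.

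**The concern.** The stratifier is the individual-provider version of the protocol's primary endpoint. Grouping on it gives strata that randomisation did not create. A provider whose pre-intervention SAR was high by chance will tend to show a reduction whether or not the feedback worked. Part of that chance may be a sicker caseload that the standardisation misses, since the SAR is adjusted through provider-level percentages of encounters with each condition. If the same unmeasured acuity raises pre-intervention readmissions, readmission will later fall among the apparent reducers with no effect at work.

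Provider fixed effects do not remove this, because they deal only with stable differences and a chance-sick period is not stable. The patient covariates help only as far as they capture acuity.

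Showing no adverse effects is a stated objective, and this contrast is aimed at the providers who cut antibiotics most. A false fall in readmission there would be taken as comfort. With no cut-off, the split could also be chosen after the data are seen.

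**Working it through.** The documents give no figure for the stratified contrast, so there is nothing of theirs to reproduce. The check asks how large an apparent SAR reduction noise alone can produce, and when that carries over to readmission.

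**Inputs from the documents**
- Spread of SAR: "interquartile range of SAR 0.9-1.1" (protocol, Background). If normal, SD = 0.2 / 1.349 = 0.148.
- Periods: "Data elements will be aggregated into 2-month intervals for each of the 147 hospitalists across each hospital" (Analysis Plan and Outcomes).
- Protocol schedule (Procedures Involved): "18 months retrospective" at baseline is nine 2-month windows, and "The intervention will last 18 months at all 4 sites" is nine more. Later hospitals have a longer baseline, so nine is the minimum before crossover.
- SAP schedule (section 3): "Following a baseline period (January 1 - June 30, 2023), the first cluster will begin the intervention on July 1, 2023". January 2023 to December 2024 is 12 windows. In Figure 1, hospitals A to D have 3, 4, 5 and 6 windows before crossover and 9, 8, 7 and 6 after, averaging 4.5 and 7.5.

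**Assumptions:** reliability of a 2-month SAR (the share of its variance that is stable between providers) of 0.85 to 0.3; independent noise between windows; large taken as the top quartile of reductions. The mean of a standard normal above its upper quartile is 1.271.

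**Step 1. Apparent SAR fall in the top quartile with no true effect**

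Fall = 1.271 × 0.148 × √(1 − reliability) × √(1/b + 1/a), with b windows before and a after. Here 1.271 × 0.148 = 0.188; √0.15 = 0.387 and √0.70 = 0.837.

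| Schedule | b, a | √(1/b + 1/a) | Fall, reliability 0.85 | Fall, reliability 0.3 |
|---|---|---|---|---|
| Protocol | 9, 9 | 0.471 | 0.034 | 0.074 |
| SAP average | 4.5, 7.5 | 0.596 | 0.043 | 0.094 |

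The SAP text allows the last hospital to cross as late as 1 March 2024. That gives averages of 4.75 and 7.25 and a fall of 0.043 to 0.093, practically the same.

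**Step 2. A fixed cut-off instead of a quartile**

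Simulation with 147 providers, large taken as a reduction of at least 10% (assumed, borrowed from the target in the Study Summary), reliability 0.3 to 0.9:

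| Windows per side | Labelled large, no true change | False SAR-change gap between strata if every provider truly falls 10% |
|---|---|---|
| 1 | 6-27% | 0.11-0.28 |
| 3 | 0.5-15% | 0.06-0.16 |
| 9 | 0-4% | 0.04-0.09 |

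In the last column about half of the providers are labelled large, although all responded identically. With no true change and nine windows, at most 0.038 × 147 = 5.6 providers are.

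**Step 3. Does this reach readmission?**

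Simulated difference-in-difference odds ratio between strata, with no true effect, 15% readmission, 30 discharges per provider-period, reliability 0.3 to 0.7 and the 10% cut-off (all assumed):
- SAR noise unrelated to readmission: OR 0.98-1.03, no material bias.
- SAR noise sharing 25-50% of its variance with unmeasured acuity worth 0.1-0.3 on the logit scale per SD: OR 0.70-0.93 with three windows per side and 0.77-0.95 with nine.

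The nine-window odds ratios describe very few providers. At reliability 0.7 only 43 to 59 simulated trials per setting gave a usable contrast, against 300 with three windows.

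**The case against.** The best defence is that the harm is conditional and the analysis marginal. Regression to the mean distorts the SAR change; it distorts readmission only through a shared cause that no passage demonstrates. Real response also shapes the strata, and averaging nine windows per side removes much of the noise. The stratification is an add-on to an all-patient analysis that it does not affect. The protocol also has semi-annual monitoring of readmission and length of stay. The SAP has its own safety models for four outcomes and a review of in-hospital deaths, none using these strata. Relating SAR change to outcomes is, moreover, a declared aim.

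All of this stands as a limit on size and importance. It does not rescue the contrast: the strata are still post-intervention, non-randomised and undefined, and the SAP's silence leaves the endpoint listed with its cut-off open.

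Two stronger readings are tempting. A reader might infer that regression to the mean alone forms the strata and that the readmission contrast is therefore certainly biased. Step 3 shows no material bias when the noise is independent of readmission. A reader might also take the SAP's 6-month baseline as three windows for everyone, pair it with the average 7.5 later windows, and get a null fall of 0.05-0.11, spanning the 10% target. That pairing fits no hospital in Figure 1: only the first has three windows before crossover, and it has nine after. The clause, moreover, belongs to the protocol, whose schedule gives smaller figures.

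**Conclusion.** The point holds as a design flaw in a listed secondary sub-analysis. The contrast between large reducers and the rest cannot support a claim of intervention effect or of safety.

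Noise alone gives the top quartile an apparent SAR fall of about 0.03-0.07 on the protocol's schedule and 0.04-0.09 on the SAP's average schedule. Around a SAR of 1, that is roughly a third to three quarters of the 10% target in the first case, approaching the target in the second only at the lowest reliability. These figures rest on the assumed reliability and on reading the published interquartile range as that of normal 2-month values. The Background does not say whether it is per provider or per provider-period; if it is per provider over the three years, window noise cannot be derived from it.

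The design flaw is clear from the text. The bias in readmission is a credible risk of unknown size: about nil without shared acuity, and falsely reassuring with it. The documents quantify neither the link nor the inputs behind the odds ratios.

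**What to change.** Remove the stratified contrast from the protocol's secondary endpoints and say so, which brings the protocol into line with the SAP.

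If safety in subgroups of prescribers is wanted, define strata from SAR or OER in windows before any hospital crosses over, with a cut-off set in advance, and test the interaction with randomised exposure. Baseline strata also regress to the mean, so the model needs stratum-by-period terms, or the windows used to form the strata must be left out of the outcome comparison.

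If the team still wants to relate SAR change to readmission, as the Background intends, label that analysis exploratory and non-causal and fix its definition of large beforehand.

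The cost is a few lines of text and, if used, one added interaction model; the plan already computes the ratios. The real downside is that baseline strata answer a different question from the association with SAR change, and leaving out the selection windows gives up some baseline data.
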